### Outcome Measures

For the primary objective of the study, patients will be clinically evaluated at the end of the treatment period with the MAS and upper FMA assessment scales, following the same procedure adopted for the initial screening. Score differences between treatment and control group will be statistically analyzed to draw conclusions on the validity and efficacy of conventional and robotic approaches to clinical treatment and assessment practices. These constitute the primary outcome measures of the study.

Regarding the secondary objective, a wide array of biomechanical- and neuromuscular activity-related features will be extracted from the NEEM torque-angle data and from the EMG signals synchronized with the exoskeleton data, respectively.

Biomechanical parameters extracted from the robot in quasi-static exercise include:

Maximum Extension Torque: the maximum torque value recorded during a static hold phase at the maximum extension angle (10);Zero Torque Angle: the angular value corresponding to null torque exerted by the robot; in this configuration, flexor and extensor torques (free of gravity force contributions) are equal and opposite and the system is ideally not applying any force to hold the elbow in position (10);Joint Impedance: measure of the total limb resistance to muscle elongation, computed as the ratio between the difference in joint torque over the corresponding change in joint angular position (33, 34); for constant, slow-speed movements, the main contribution to the joint impedance can be identified in the joint stiffness (i.e., rigidity).EMG signals recorded during quasi-static exercises are used as reference for the background muscle activation, where no spastic contractions should be elicited.

Biomechanical parameters extracted from the robot in passive exercises include Maximum Extension Torque, Zero Torque Angle and Joint Impedance (in this case also including a velocity-dependent viscoelastic component). Additionally, the normalized Torque-Angle Integral is extracted: the integral of the Torque-Angle curve, normalized to the pROM, represents a measure of the expended energy by the robot to move the patient's arm. Higher values correspond to limb stiffening, as the exoskeleton delivers more power to mobilize the limb in the ROM.

For the active exercises, the main outcome measure is the movement smoothness: recently, several studies (35, 36) have approached the question of how to classify and quantify movement “smoothness.” Unequivocally, healthy subjects show faster, more continuous movements compared to patients affected by neural deficits (37).

In addition to biomechanical parameters, other features are extracted from EMG signals during passive and active exercises (10):

- Stretch Reflex Onset: extrapolated from the EMG envelope, it is defined as the first sustained burst of muscular activity above the baseline value for at least 200 ms. The threshold for muscle activation is defined as the *mean*+*2*^*^
*standard deviation* value of the filtered EMG signal in the 100 ms time window prior to the imposed stretch (38);- EMG Burst Duration: percentage of the F/E movement time during which EMG activity is present (39);- Position Threshold: defined as the joint angular value associated to the Stretch Reflex Onset (10, 38);- Muscle Co-activation: defined as the percentage of movement time in which simultaneous activation of agonist and antagonist muscles (i.e., BB and TB) is observed.

EMG outcomes will be interpreted with biomechanical parameters, with the goal to provide a comprehensive description of the biomechanical and neurophysiological components of joint resistivity. Finally, robotic and clinical measures will be investigated to provide a more detailed clinical picture of each patient by enriching the information content of the assessment scales.

### Statistical Analysis

In addition to descriptive statistics characterizing the study population and the assessment of potential clinical or demographic differences between groups via Pearson's chi-squared test, this study will employ a paired one-way analysis of variance (ANOVA) of all primary outcome measures, with repeated measures taken from baseline (T0) and post-treatment (T1). This series of tests will be contingent on confirmation of the normality of all data distributions using the Shapiro-Wilk normality test. If data are found not to conform to the null hypothesis of Gaussian distribution, then the parametric Mann–Whitney *U*-test (also known as Wilcoxon rank sum test) will be used in place of ANOVA, in pair-wise fashion.

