## Materials and Methods

### Objectives

The primary study objective is to rigorously evaluate the efficacy of robotically assisted training as a novel modality for clinical rehabilitation of post-stroke elbow spasticity and motor function, in a randomized controlled trial relative to conventional physical therapy. Secondarily, the study aims to validate a novel instrumented method for elbow stiffness/spasticity evaluation, by combining biomechanical (robotically recorded) and electromyographic (EMG) parameters.

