### Participants and Recruitment

All procedures conform to the Declaration of Helsinki and have been approved by the Ethical Committee for the Azienda USL Toscana Nord Ovest (AUSLTNO) and the Italian Ministry of Health.

The study is conducted at the Recovery and Functional Rehabilitation department of Ospedale Versilia (Lido di Camaiore, Italy), in collaboration with The BioRobotics Institute of Scuola Superiore Sant'Anna. It involves 60 post-stroke patients with right-sided hemiplegia, randomly allocated either to the control (*n* = 30) or treatment (*n* = 30) group. The sample size of each group was calculated based on the hypothesis of a post-treatment MAS score reduction of 0.5 points (compared to pre-treatment, from an average of 2.5 ± 0.70 SD at baseline) with an alpha value of 0.05 and power equal to 80%. (30).

According to inclusion criteria, patients should: (1) be in the age range 18–79; (2) have sustained unilateral hemorrhagic or cerebro-vascular ischemic event in sub-acute (< 6 months) or chronic (> 6 months) phase; (3) experience a functional motor deficit of the right arm (ranging from mild to severe hemiplegia or paresis); (4) have residual cognitive capabilities sufficient for the understanding of basic instructions (Mini-Mental State Examination score > 24); (5) exhibit lack of pain upon passive mobilization of the limb; (6) be able to sign an informed consent. On the contrary, patients are excluded from the study in case of: (1) unstable state of general health; (2) inability to remain in a seated position for a prolonged period (1 h or more); (3) use of a cardiac pacemaker or other active implanted medical devices; (4) passive range of motion (ROM) lower than 10 degrees. In addition, patients who received botulinum toxin injections within 3 months prior to the participation to the study or individuals who follow any additional pharmacological treatment that may alter the outcome of the study are excluded from the participation to the study. Sudden changes in subjects' health conditions, severe alterations in their psychophysical well-being or the inability to attend more than three daily consecutive sessions will lead to the exclusion from the study.

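### The only parametric test named for MAS and FMA is a within-patient T0–T1 comparison, which contradicts the stated comparison of robot with control, and its fallback does not match it

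*Protocol article*

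**What the plan says.** The Objectives section asks for the efficacy of robot-assisted training "in a randomized controlled trial relative to conventional physical therapy". The Study Protocol Design section describes two randomised arms with matched therapy volume. Outcome Measures adds, for MAS and FMA: "Score differences between treatment and control group will be statistically analyzed". It names no test.

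Tests are named only under Statistical Analysis:

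- **Primary outcomes:** a "paired one-way analysis of variance (ANOVA) of all primary outcome measures, with repeated measures taken from baseline (T0) and post-treatment (T1").
- **If Shapiro-Wilk rejects normality:** the "Mann–Whitney *U*-test (also known as Wilcoxon rank sum test) will be used in place of ANOVA, in pair-wise fashion".
- **Between groups:** "assessment of potential clinical or demographic differences between groups via Pearson's chi-squared test". This concerns patient characteristics, not the outcomes.

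The sample-size statement in Participants and Recruitment is also worded within patients: a "post-treatment MAS score reduction of 0.5 points (compared to pre-treatment, from an average of 2.5 ± 0.70 SD at baseline"). The same sentence sets the significance level at 0.05 and the power at 80%; each arm has 30 patients.

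**The concern.** A one-way repeated-measures ANOVA has one factor, and here that factor is visit. It contains neither treatment group nor a group-by-time term. It tests whether scores moved between T0 and T1, not whether they moved more with the robot.

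Both arms receive four weeks of active therapy, and sub-acute patients are eligible, so change common to both arms is possible. A pre-post test cannot separate that change from an effect of the exoskeleton.

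The fallback adds a second problem. Mann-Whitney compares independent groups, whereas the ANOVA it replaces compares repeated measurements on the same patients. Without a definition of the pairs, the analysis could move from a within-patient to a between-arm question, or misuse an independent-samples test on paired data, depending on the Shapiro-Wilk result.

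**Working it through.** **Inputs from the article:** 30 per arm; MAS SD 0.70 at baseline; change of 0.5 points; alpha 0.05; power 80%.

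**Assumptions:** two-sided testing; the same SD at T0 and T1; normal data; T0–T1 correlation ρ of 0, 0.5 or 0.7. The article gives neither ρ nor the SD of change.

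**1. The stated sample size.** The two-independent-samples normal formula gives

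n = 2 × 0.70² × (1.960 + 0.842)² / 0.5² = 0.98 × 7.85 / 0.25 ≈ 30.8, so 31 per group.

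This is close to the stated 30, where power is 79.0% (normal approximation) or 77.6% (t-test). A paired formula with SD of change 0.70 × √(2(1 − ρ)) gives 31, 16 and 10 at ρ = 0, 0.5 and 0.7. The stated 30 therefore fits a two-sample formula, or a paired one with ρ = 0, although the hypothesis is worded as pre-to-post.

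**2. The named test when the robot adds nothing.** Let both arms improve by 0.5 points, so the true between-arm difference is zero.

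| ρ | SD of change | Robot-arm T0–T1 test significant (n = 30) | Pooled T0–T1 test significant (n = 60) | Between-arm test of change significant |
|---|---|---|---|---|
| 0 | 0.990 | 76% | 97% | 4.9% |
| 0.5 | 0.700 | 97% | over 99.9% | 4.9% |
| 0.7 | 0.542 | 99.8% | 100% | 5.0% |

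The T0–T1 columns come from paired-t power and agree with 20,000 simulated trials per row. The last column is from those simulations.

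With a smaller shared gain of 0.25 points, the robot-arm test is significant in 27%, 47% and 68% of trials at the three correlations.

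**3. What 30 per arm gives for a between-arm difference of 0.5.** The SD for change scores is 0.70 × √(2(1 − ρ)). With baseline adjustment it is 0.70 × √(1 − ρ²).

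| ρ | Change scores: SD, power | n per arm for 80% | Baseline-adjusted: SD, power | n per arm for 80% |
|---|---|---|---|---|
| 0 | 0.990, 49% | 63 | 0.700, 78% | 32 |
| 0.5 | 0.700, 78% | 32 | 0.606, 88% | 25 |
| 0.7 | 0.542, 94% | 20 | 0.500, 97% | 17 |

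**The case against.** The intent to compare arms is on the page. Outcome Measures promises a treatment-versus-control analysis, the Mann-Whitney fallback could be run between arms, and 30 per arm fits a two-sample formula. MAS is ordinal, so Shapiro-Wilk may well reject and make the fallback the working test for that scale. A reader might infer from the ANOVA sentence that the trial discards its randomisation, or that a result significant in the robot arm but not in control will be taken as efficacy. The documents support neither inference: the article commits to a between-arm comparison and nowhere states such a decision rule.

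Shared improvement in MAS is also an assumption. The Introduction and Discussion describe post-stroke spasticity as typically increasing, and the Discussion cites a randomised pilot in which elbow MAS did not improve significantly on conventional therapy alone.

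Nor should weight be put on how often only the robot arm would be significant. With a shared gain of 0.25 points this is about 20% to 25%, but that is near the ceiling, since p(1 − p) cannot exceed 0.25. With a shared gain of 0.5 it is 18%, 3.3% and 0.2% at ρ = 0, 0.5 and 0.7.

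What does not stand is the suggestion that these passages repair the analysis section. Outcome Measures names no test, and a fallback that applies only when normality fails cannot supply the comparison when it holds. Nor is this a detail left to an analysis plan: a specific test is stated, and it does not fit the objective. If a group-by-time ANOVA was meant, the description as one-way is wrong and needs correcting.

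**Conclusion.** The point holds as a contradiction within the article: the one parametric test named for the primary outcomes cannot estimate the difference that the Objectives, Study Protocol Design and Outcome Measures sections call for, and the fallback does not match the test it replaces. It should be corrected before analysis.

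The size given, 76% to 99.8% against about 5%, is conditional on a shared 0.5-point gain, equal SDs of 0.70, normal data and the assumed correlations. It shows how little a T0–T1 test says about the robot's added effect; it does not forecast this trial's result. Because MAS is ordinal, the figures are illustrative. The mismatch between test and objective depends on none of these assumptions.

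**What to change.** 1. **Primary analysis.** State, for MAS and for FMA, that the treatment and control groups are compared at T1 with adjustment for the T0 score of the same scale, and that the between-arm difference with its 95% CI is the primary result. Stroke phase is an optional covariate. FMA level is not needed when FMA is the outcome, because it is a cut of the T0 FMA score. A group-by-time term in a two-arm, two-visit model would also remove the contradiction.
2. **Fallback.** Remove the Shapiro-Wilk switch, or define the rank alternative as a between-arm test on T0–T1 change.
3. **Within-arm changes.** Report them as descriptive only.
4. **Sample size.** Restate the 0.5-point hypothesis in Participants and Recruitment as a between-arm difference, with the assumed SD or correlation and the resulting power. At 30 per arm and correlation 0 / 0.5 / 0.7 this is about 78% / 88% / 97% with baseline adjustment, or 49% / 78% / 94% for change scores.

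The cost is rewording two sections. T0 and T1 scores are already measured in both arms, and stroke phase is known from eligibility. The restated power may show that 30 per arm falls short of 80% if the correlation is low, and it is better to state that now than to discover it at analysis.

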For instance, in a randomized pilot study (*n* = 30), Fazekas et al. (9) employed passive mobilization of the shoulder and elbow via two industrial robots in patients with upper limb hemiparesis due to stroke or mild traumatic brain injury, with results demonstrating significant clinical improvements in elbow MAS with combined robotic-plus-conventional therapy, but not conventional therapy alone. Similarly, Posteraro et al. (41) employed a planar end-effector robot (MIT-MANUS) in a 10-session rehabilitation protocol, finding statistically significant improvements in the shoulder MAS, elbow passive ROM, and Motor Status Score at both the shoulder and elbow using two separate treatment protocols focusing on different movement patterns. By contrast, the stretch reflex—evaluated indirectly via the robotic parameter of minimum jerk deviation as an indicator of spasticity—showed no statistically significant decrease for either treatment protocol.

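### The parametric test named for the primary outcomes has time as its only factor, so it does not match the between-arm comparison announced, and the rank fallback does not say what it compares

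*Protocol article*

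**What the plan says.** **Objective and announced comparison.** The Objectives section sets the efficacy question "in a randomized controlled trial relative to conventional physical therapy". Outcome Measures, on MAS and FMA, says "Score differences between treatment and control group will be statistically analyzed to draw conclusions on the validity and efficacy of conventional and robotic approaches". Both describe a contrast between the arms, and neither names a test.

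**Named tests.** Statistical Analysis names three:
- for group characteristics, "assessment of potential clinical or demographic differences between groups via Pearson's chi-squared test";
- for the primary outcomes, a "paired one-way analysis of variance (ANOVA) of all primary outcome measures, with repeated measures taken from baseline (T0) and post-treatment (T1");
- if normality is rejected, the Mann–Whitney U-test, "also known as Wilcoxon rank sum test) will be used in place of ANOVA, in pair-wise fashion".

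**Sample size.** Participants and Recruitment bases 30 per group on a "post-treatment MAS score reduction of 0.5 points (compared to pre-treatment, from an average of 2.5 ± 0.70 SD at baseline"), with alpha 0.05 and 80% power. The effect is worded as a change from pre-treatment, not as a difference from control.

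**The concern.** A one-way analysis has one factor. Because it is described as paired and repeated over T0 and T1, that factor is time. With two time points it is the paired t-test, whether run within each arm or over all 60 patients. It cannot estimate or test a difference between arms.

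The fallback does not settle the matter. Mann–Whitney is a two-sample test, but here it stands in for a T0–T1 test and is applied pair-wise, with the samples unnamed. It could compare arms at T1, arms on change, or T0 with T1. The Introduction describes MAS as ordinal, so the fallback may well be the test actually used.

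Both arms receive four weeks of therapy and sub-acute patients are eligible, so a gain common to both arms is possible. If the robot's efficacy were read from a T0–T1 test, or from significance in one arm and not in the other, such a gain could be credited to the robot. The error rate of that inference is not 5%.

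**Working it through.** **Inputs from the article:** 30 per arm; MAS change 0.5; baseline SD 0.70; alpha 0.05; power 80%.

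**Assumptions (not in the article):** two-sided alpha; T0–T1 correlation ρ from 0 to 0.7; equal SD at T0 and T1; normal data; no dropout; a shared gain of 0.25 as a second scenario.

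**1. The plan's own figure.**
- Two independent means: n = 2 × [0.70 × (1.960 + 0.842) / 0.5]² = 30.8, so 31 per arm (32 with the t distribution). Power at 30 per arm is 79.0% (normal) or 77.6% (t). The stated 30 is therefore reproduced to within two patients.
- Pre-post change: SD of change = 0.70 × √[2(1 − ρ)] and n = [SD of change × 2.802 / 0.5]². This gives 31, 22, 16 and 10 at ρ = 0, 0.3, 0.5 and 0.7.

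So 30 fits a two-sample formula, or a pre-post formula that ignores within-patient correlation. The arithmetic alone does not show which was meant.

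**2. No true arm difference: how often is each test significant?** Results are from 20,000 simulated trials per row. For the robotic arm, the noncentral-t calculation agrees: noncentrality = 0.5 × √30 / SD of change, for example 0.5 × 5.477 / 0.70 = 3.91 at ρ = 0.5, which gives 96.6%.

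| Shared gain | ρ | SD of change | Robotic arm, T0–T1 | All 60 pooled, T0–T1 | Robotic significant, control not | Between-arm test of change |
|---|---|---|---|---|---|---|
| 0.5 | 0 | 0.990 | 76% | 97% | 19% | 5.0% |
| 0.5 | 0.3 | 0.828 | 89% | 99.6% | 10% | 4.9% |
| 0.5 | 0.5 | 0.700 | 97% | 99.98% | 3% | 4.8% |
| 0.5 | 0.7 | 0.542 | 99.8% | 100% | 0.2% | 5.1% |
| 0.25 | 0 | 0.990 | 27% | 49% | 20% | 4.9% |
| 0.25 | 0.3 | 0.828 | 36% | 63% | 23% | 5.2% |
| 0.25 | 0.5 | 0.700 | 47% | 78% | 25% | 5.0% |
| 0.25 | 0.7 | 0.542 | 68% | 94% | 21% | 5.0% |

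The discordance column is close to p(1 − p), where p is the robotic-arm column. It peaks at 25% when p is near one half, so the 0.25 scenario lies close to the worst case. At the article's own 0.5 it falls steeply as ρ rises.

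**3. Power of a between-arm test at 30 per arm**, if the true between-arm difference were 0.5 (an assumption, since the article's 0.5 is pre-post). The SD is 0.70 × √[2(1 − ρ)] for change and 0.70 × √(1 − ρ²) for T1 adjusted for T0.

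| ρ | Change | T1 adjusted for T0 |
|---|---|---|
| 0 | 49% | 78% |
| 0.3 | 63% | 81% |
| 0.5 | 78% | 88% |
| 0.7 | 94% | 97% |

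**The case against.** **A reader might infer that the randomised comparison is never tested.** The article does not support that. Outcome Measures commits to analysing score differences between the arms for the primary outcomes. What is missing is a named test that does so.

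**A reader might infer that the paired ANOVA is the only primary test.** It is not. The Mann–Whitney test is also named and compares independent samples, so it is some evidence that an arm comparison was intended. A sample size that fits a two-sample formula points the same way. The samples remain unstated, and the effect is worded as pre-post, so the ambiguity stands.

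**A reader might infer that a T0–T1 test will come out positive whatever the robot does.** The article gives no control-arm MAS gain. The Introduction and Discussion describe spasticity as typically increasing after stroke, and chronic patients are also eligible. A shared gain is possible, not established.

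**The Discussion cites an earlier trial with "significant clinical improvements in elbow MAS with combined robotic-plus-conventional therapy, but not conventional therapy alone".** That passage is about another study. It shows the form a within-arm inference takes, not that this trial will draw one.

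**An article condenses the full protocol, and a separate analysis plan may hold the detail.** That would excuse silence about the contrast. It does not excuse naming a specific test that answers a different question.

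**The calculations treat MAS as continuous and omit the normality check.** True. They show the direction and rough size of the problem, not exact rates for this trial.

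**Conclusion.** The point holds as an inconsistency between sections. The parametric test named in Statistical Analysis has no arm factor and cannot deliver the comparison set out in Objectives and Outcome Measures, and the fallback does not say which samples it compares. This is a wrongly stated analysis rather than missing detail.

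The size depends on how the result would be used. If efficacy were read from the robotic arm's T0–T1 test, an equal 0.5-point gain in both arms would give a significant result in 76% to 99.8% of trials, against about 5% for a between-arm test. If it were read from significance in the robotic arm only, the rate is 19% falling to 0.2% at a shared gain of 0.5, and 20% to 25% at an assumed shared gain of 0.25. These figures rest on the assumed correlation range, two-sided 5%, equal SDs of 0.70, normal scores and no dropout. Nothing in the article says that efficacy will be inferred in either way, but as written the named analysis does not prevent it.

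**What to change.** In Statistical Analysis:
- Replace the paired one-way ANOVA with a between-arm test for each primary scale, reported with a 95% CI. Preferably compare T1 between arms adjusted for T0. The arm-by-time term, equal to the between-arm comparison of change, is valid but has less power at every correlation examined.
- If a rank method is kept, state that it compares change between arms.
- State that within-arm T0–T1 changes are descriptive.

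In Participants and Recruitment, say plainly that the 0.5-point effect is pre-post, or restate it and the power for the between-arm contrast.

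The cost is one paragraph of analysis wording and a sentence or two on sample size, with no new data. Whether 30 per arm is enough cannot be settled from the article. For an assumed between-arm difference of 0.5, the adjusted comparison has 78% power at ρ = 0 and exceeds 80% from ρ = 0.3, whereas the change score is still at 78% at ρ = 0.5.
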